# Transpalpebral electrical stimulation for the treatment of retinitis pigmentosa: study protocol for a series of N-of-1 single-blind, randomized controlled trial

**DOI:** 10.1186/s13063-024-07933-0

**Published:** 2024-01-27

**Keywords:** Transpalpebral electrical stimulation, Microcurrent stimulation, Retinitis pigmentosa, N-of-1 trial

## Abstract

**Background:**

Retinitis pigmentosa (RP) is an inherited disease characterized by a progressive loss of rod photoreceptors of the eye, leading to irreversible blindness. To date, to our knowledge, no clinical prospective studies have been undertaken that could document the effect of interventions that could reverse or reduce the progression of this disease. The application of microcurrent stimulation (ES) of the eye in the treatment of chronic eye diseases such as glaucoma and age-related macular degeneration has been used over several decades and has been reported to have beneficial effects to reduce the progression of these blinding diseases and has been supported by animal studies and smaller clinical studies, but to date, no large randomized clinical trials on the use of microcurrent therapy have been published. More recent clinical reports have also shown beneficial effects of ES on slowing the progression of RP but also lacks data from robust prospective clinical outcome studies. To our knowledge, this is the first prospective randomized study to evaluate the safety and clinical effectiveness of transpalpebral electrical stimulation (TpES) on the progression of RP.

**Methods:**

Randomized prospective study using N-of-1 trial 3 single-blind, crossover comparisons. The intervention period of each comparison is divided into treatment period and control period which are randomized arranged. Twelve participants will be strictly recruited in N-of-1 trial by the researcher in accordance with the inclusion and exclusion criteria. The main outcome of interest examined after each cycle of the 8-week intervention period is the assessment of the visual field (VF). Other variables of interest are best corrected visual acuity (BCVA), retinal function using electroretinogram (ERG), and visual function using NEI VFQ-25 questionnaire. Objective assessments of retinal changes will be undertaken using optical coherence tomography (OCT) and fundus autofluorescence (FAF).

**Discussion:**

The trial will evaluate the efficacy and safety of microcurrent stimulation on RP and provide high-quality evidence for clinical application through N-of-1 trial.

**Trial registration:**

Chinese Clinical Trial Registry; ChiCTR2300067357; https://www.chictr.org.cn/showproj.html?proj=174635. Registered on 5 January 2023

**Supplementary Information:**

The online version contains supplementary material available at 10.1186/s13063-024-07933-0.

## Introduction

Retinitis pigmentosa (RP) refers to a group of inherited retinal diseases that most often leads to severe visual impairment and blindness. Forms of RP and related diseases include Usher syndrome, Leber congenital amaurosis, and Bardet-Biedl syndrome among others. It is estimated that about 1.5 million people are affected by RP worldwide [1]. RP is the most common type of inheritable degenerative retinal disorder with an incidence of approximately 1/5000 ~ 1/3500 [2]. In China, the prevalence is about 1/4000, with the ratio of male to female is 3:2. RP is commonly divided into autosomal dominant, autosomal recessive, and X-linked inherited disease. It is characterized by progressive loss of retinal photoreceptor cells and retinal pigment epithelial (RPE) cells. The loss of rods photoreceptors precedes the loss of cone photoreceptors. The loss of photoreceptors results in the progressive impairment of night vision and of visual field (VF). Fundus examination shows typical “osteocytic” pigmentation, constriction of retinal vessels, and waxy pallor of optic disc [3]. Visual impairment develops typically already in the second or third decade of life with rapid progression to severe visual impairment before the age of 50, which leads to a serious negative impact on patient’s work and life, as well as economic and mental burden on family and society. The exact pathogenesis is unknown. A wide variety of experimental research is currently being conducted, such as possibilities for correcting the genetic defects of RP through gene carrier transfer [4], promoting the differentiation and maturation of RPE cells by stem cell transplantation [5], delaying the apoptosis of photoreceptor cells by neurotrophic factor [6], and inducing the electrical activity of retina and visual cortex by retinal prosthesis implantation [7]. These applications have yet to be applied clinically.

In 2004, when Chow and his team were investigating the safety and efficacy of the artificial silicon retina microchips implanted in the subretinal space, they discovered that low electric current could reduce and even reverse the loss of retinal function in RP, restoring the VF [5]. Since then, the application of electrical stimulation (ES) in the treatment of ophthalmic diseases has been widely studied. ES has shown to play a neuroprotective role in retinal diseases by improving both cerebral and ocular microcirculation. ES has shown to increase blood flow in both the optic nerve and retina [8, 9]. Studies have also shown that ES improves blood circulation of retinal choroid [10, 11], resulting in slowing the process of disease progression that ultimately leads to apoptosis of photoreceptor cells. ES has also shown to promote the growth of synapses and the survival of neurons, to activate retinal neurons to produce neural electrical activity, and to promote the transmission of photoelectric signals between neurons, resulting in the improvement of visual function [12, 13]. ES has been shown to stimulate glial cells to release neuroprotective factors, such as brain-derived neurotrophic factor and ciliary neurotrophic factor. Moreover, it can inhibit the expressions of tumor necrosis factor alpha and interleukin 1β, thus inducing apoptosis and inflammation. Therefore, there may exist multiple mechanisms for neuroprotection [14, 15].

In our own studies, we observed the effect of transpalpebral electrical stimulation (TpES) on both RP mice models and on RP patients had great potential to improve visual function. If applied properly, TpES may be a convenient and noninvasive therapy in regenerative medicine. To further verify the efficacy and safety of TpES treatment, we have designed this prospective N-of-1 single-blind, randomized controlled trial.

## Methods

### Objectives

The aim of this study is to evaluate the efficacy and safety of TpES in the treatment of RP and to provide high-quality evidence for clinical application through N-of-1 trial.

### Study design

This is a prospective, comparative, and single-blind N-of-1 trial, which includes 3 crossover comparisons. Each comparison includes an 8-week treatment period (A) and an 8-week control period (B). According to the random number generated by Strategic Applications Software (SAS), the random arrangement of AB or BA is presented in each cycle (Fig. 1).

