#### Randomization and blinding

Allocation of cases to study groups is undertaken by a person not participating in the trial with the help of the generation of random sequencing using the SAS statistical software. Allocations are placed in sealed envelopes. Participants will be allocated an individual trial identification number. Research assistants will perform the allocation of patients to the study groups by opening of sealed envelopes at the time and prior to the first intervention cycle.

Due to the nature of the intervention, only the principal investigator is blinded to the treatment in this study. Unblinding is permissible only if the intervention is considered necessary to guide clinical management and with the consent of the principal investigator.

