### Sample size

The sample size was calculated from SUN’s previous study [16]. The primary outcome was the change of mean defect (MD) value of VF after 8 weeks of treatment compared with baseline. Based on the reference (Sun et al.), the MD value of the treatment group is 2.06 ± 1.73. The MD value of the control group is 0.73 ± 1.93. The difference between the effect values of the treatment period and the control period was 1.43, and the standard deviation of the two periods was 1.93. When a two-tailed test with a test power of 80% and significance level of 5% was applied to the research, 10 cases were calculated [17]. Taking into account of 20% dropout rate, we ultimately identified 12 participants.

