### Statistical analysis

Statistical analysis will be performed by Statistical Package for the Social Sciences (SPSS) for version 25.0. Descriptive statistics will be used to analyze demographic characteristics of participants, including age and gender. Continuous variables will be presented as mean ± standard deviation. The primary and secondary outcomes will be analyzed using the full analysis set. Each patient’s paired trial is treated as an independent trial. For the in-group effects, the paired *t*-test is used for the data with normal distribution, and the Wilcoxon rank sum test is used for the data with non-normal distribution. For the intergroup effect, three pairs of data with normal distribution will be used with repeatability measure ANOVA test, and linear mixed-effects model will be used with non-normal distribution. For missing values, we will use a mixed-effects model for repeated measures. The *P* (2-tailed) value with threshold less than 0.05 will be considered statistically significant.

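### No stated balance of AB and BA order and no period term for normal data: a small precision cost to the pooled test, a larger problem for individual results

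*Protocol article*

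**What the plan says.** The Study design section of the protocol article describes a trial "which includes 3 crossover comparisons", each made up of an 8-week treatment period (A) and an 8-week control period (B). Using SAS random numbers, "the random arrangement of AB or BA is presented in each cycle". The Randomization and blinding section adds that the sequence is generated in SAS by someone outside the trial and released by "opening of sealed envelopes at the time and prior to the first intervention cycle". Neither section states a block, stratum or other restriction on order.

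The Statistical analysis section says that each patient's "paired trial is treated as an independent trial". It continues: "For the in-group effects, the paired *t*-test is used for the data with normal distribution", with a Wilcoxon test otherwise. For the intergroup effect it names a repeated-measures ANOVA on three pairs for normal data and a linear mixed-effects model for non-normal data. A mixed model for repeated measures is named for missing values. No terms are listed for either mixed model.

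The Discussion justifies the N-of-1 design by the need to judge the effect in the individual patient. It counts as a strength that the effect can be read within each cycle, without waiting for the end of the trial. It also calls RP chronic and progressive.

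**The concern.** In one participant's cycle, the A-B difference contains the treatment effect plus or minus whatever differs between the first and second period of that cycle, such as disease progression or perimetry practice. Over many cycles this cancels only to the extent that AB and BA occur equally often, or that the analysis removes it. The article states no means of making the counts equal. For normal data, it names tests that cannot remove the difference: a paired t-test has no place for it, and an ANOVA on three pairs can carry cycle but not position within a cycle.

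Two things are at stake. In the pooled comparison, an uneven split shifts the estimate of that particular trial, and the unmodelled difference adds noise. In a single participant, three cycles can never split evenly, so part of any period difference always stays in the crude mean. If all three cycles have the same order, all of it stays.

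**Working it through.** **Inputs.** From Sample size: effect 1.43, SD of a period 1.93, two-sided 5%, power 80%, 10 participants before dropout and 12 after. From Study design: 3 cycles, so 12 × 3 = 36 pairs. The effect of 1.43 is used as stated, although the group values given there differ by 2.06 − 0.73 = 1.33. Assumed, because the article gives no such figure: a period difference π (second minus first period of a cycle) of 0.5 to 1.0 on the MD scale, with larger values shown for scale; independent 50:50 draws; pairs independent, as the article treats them.

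**The plan's own figure.** Taking 1.93 as the SD of one period, a pair difference has SD 1.93 × √2 = 2.73 and variance 7.45. Pairs needed = (1.960 + 0.842)² × 7.45 / 1.43² = 28.6, so 29. Then 29 / 3 = 9.67, so 10 participants, as stated. This SD is used below.

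**Order imbalance over 36 pairs (binomial).**
- Exactly 18:18: 13%.
- 21:15 or worse: 41%, a shift of at least π × 6/36 = 0.17π.
- 24:12 or worse: 6.5%, a shift of at least π × 12/36 = 0.33π.
- Expected shift 0; SD π/√36 = π/6, which is 0.08 for π = 0.5 and 0.17 for π = 1.0.

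**Variance.** The unmodelled difference adds π² to the pair-difference variance: 0.25/7.45 = 3% for π = 0.5 and 1.00/7.45 = 13% for π = 1.0.

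**Type I error.** In simulation (40,000 trials), the unadjusted paired t-test on 36 pairs rejects in 4.8 to 5.0% of null trials for every π from 0 to 3. Among trials split 24:12 or worse in one direction, it rejects in about 6% (π = 0.5) or 10% (π = 1.0).

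**Power for 1.43 (simulation, 20,000 trials per row).**

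| π | Independent draws, paired t-test | Independent draws, one first-versus-second term | Independent draws, six-level period | Balanced list, six-level period |
|---|---|---|---|---|
| 0 | 86% | 85% | 83% | 86% |
| 0.5 | 85% | 85% | 83% | 86% |
| 1.0 | 82% | 85% | 83% | 86% |
| 1.43 | 77% | 85% | 83% | 86% |

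**Individual participants.** Of the 2³ = 8 possible three-cycle sequences, 2 repeat one order throughout, so the probability is 2/8 = 25%. The expected number is 12 × 0.25 = 3, and the chance of at least one is 1 − 0.75¹² = 97%. In such a participant, the crude mean A-B difference is shifted by the whole of π (0.5 to 1.0). In the other 75%, the split is 2:1 and the shift is π/3 (0.17 to 0.33).

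**The case against.** The strongest reply is that a condensed article may leave restrictions on the list and model terms to the full protocol or analysis plan, so silence is not evidence of absence. This stands in part. A reader might infer that the order is unbalanced and that no analysis includes period, but the documents show only that no balance is stated, and the mixed models list no terms. The reply does not cover the tests named for normal data, which leave no room for a within-cycle period term.

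It also stands that random order is itself protection. A reader might infer that the treatment estimate is biased. Over the randomisation the expected shift is zero and the error rate holds, so that reading fails.

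A reader might also take "The MD value of the control group is 0.73 ± 1.93" as proof of a sizeable drift without treatment. The article does not say that those controls were untreated. The figure is a change within one group, not a difference between the two periods of a cycle. It also lies in the same direction as the planned benefit, whereas progression would run the other way. If each period were scored from its own start, a steady trend would largely cancel. The size of π therefore remains an assumption.

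Finally, a single cycle of 12 splits 8:4 or worse 39% of the time, but that does not describe the pooled analysis. Over 36 pairs, an equally uneven split has probability 6.5%.

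**Conclusion.** The point holds as a modest one for the pooled comparison and a more serious one for individual results. For π of 0.5 to 1.0, the pooled estimate shifts with SD 0.08 to 0.17 against a planned effect of 1.43, pair-difference variance rises 3 to 13%, and power falls from about 86% to no lower than about 82%. Type I error over the randomisation is unaffected.

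For individuals, about 3 of 12 participants would repeat one order in all three cycles. Their own data cannot separate treatment from a consistent first-versus-second difference unless a shape is assumed for the trend over the six periods. This matters because the article rests its choice of design on individual evaluation.

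The conclusion assumes independent 50:50 draws, which the article neither confirms nor excludes, a period difference common to all participants, and a pair-difference SD of 1.93 × √2. If the full protocol already restricts the order, the imbalance part falls away and only the period term remains to be settled.

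**What to change.** 1. State whether the SAS list restricts the order.
2. For participants not yet allocated, drop AB-AB-AB and BA-BA-BA and give each of the six remaining sequences to two participants. This yields 6:6 in every cycle and 18:18 overall.
3. In every case, replace the plain paired t-test on MD with a model that has treatment and period as fixed effects and keeps the pairing within participant and cycle.

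There are no extra patients, visits or tests. With the balanced list, the period term costs essentially no power. If the order is left unbalanced and there is no period effect, it costs about 1 point as a single first-versus-second term or about 3 points as a six-level factor. The single term may therefore be preferable if allocation is already complete, which is possible since the Trial status section expects recruitment to end in March 2024. Dropout, planned at 20%, may disturb the exact balance, and the period term then handles it. No list of three cycles balances within a participant: a third of π stays in each crude individual mean, so individual results should also be reported with period adjustment from the joint model.

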**Fig. 1 Fig1:**

Example of N-of-1 trial design

#### Interventions

The operation procedure is as follows: (1) connect the device before preparing for treatment, and check whether the device is adequately powered. (2) Participants are asked to close their eyes. The electrodes and wet cotton pads soaked in pure water are then applied to the eyelids and the headband is fixed.

#### Study period of treatment (TpES intervention)

For the period of treatment, TpES is applied to both eyelids twice a day for 5 min each time. The current intensity is set to 0 ~ 800 μA. The 5-min protocol is comprised of a biphasic pulse with a frequency of 292 Hz for 30 s, 30 Hz for 30 s, 9.1 Hz for 2 min, and 0.3 Hz for 2 min. The participants should turn on the microcurrent device themselves and adjust the device’s current intensity knob so that the flash sensation just appears (Fig. 2).

**Fig. 2 Fig2:**
[figure not shown]
The microcurrent device and transpalpebral electrical stimulation

#### Study period of control (no TpES intervention)

A TpES device is applied to the eyelids, but no electrical stimulation is given, and no pulsation is felt. Everything else remains the same.

During treatment and control periods, other treatments for RP will be discontinued, such as complementary therapies (herbal remedies and acupuncture) or other medications, throughout the study. Participants can take Western medicine to treat systemic diseases, such as hypertension or hyperlipidemia. Medication use will be recorded in detail in the case report form (CRF).

### Recruitment of research subjects

The subjects to be included for this study are RP patients recruited from the outpatient department of Eye Hospital, China Academy of Chinese Medical Sciences. This is a large hospital in Beijing, China, that sees many outpatients on a daily basis, offering both conventional treatment of eye diseases as well as traditional Chinese medicine and diverse energy treatments. RP is a rare eye disease. To enroll a sufficient number of participants, patients meeting the requirements for inclusion criteria were considered before the beginning of the study. The eligible patients will be notified as soon as the relevant procedures of the clinical trial are completed. Besides, we will post the recruitment posters through social media and other channels. Upon inclusion into the study, informed consent will be given with introduction of the details of the trial protocol including detail information about the treatment with its benefits and risks. Participants must sign an informed consent form prior to the study. Both the investigator and participants retained an informed consent form.

#### Eligibility

Inclusion criteriaFulfill diagnostic criteria of RPAged between 18 and 80 years oldThe best corrected visual acuity (BCVA) of at least one eye is greater than or equal to 35 letters detected on the ETDRS acuity chart (equal to 20/200 on Snellen chart)VF radius of one eye is greater than 5° with the grayscale images of VFSubjects agree to participate in the study and sign the informed consent form

Exclusion criteriaPatients with known adverse reactions to ocular ESPatients with other eye diseases such as optic nerve diseases, glaucoma, macular edema not caused by RP, diabetic retinopathy, ocular autoimmune diseases, and ocular surface diseases affecting visual functionPatients who are considered by the investigators to be unable to provide reliable VF results in static or dynamic VF examinations. The value of reliability factor is greater than 15%Mental illness or cognitive impairment and other disorders affecting research and follow-upPatients with pacemakersParticipating in other clinical trials within the last 3 months and other therapies that affect the evaluation of efficacyPregnant and lactation women, and those who are hoping to become pregnant during the trial period

#### Termination criteria

If serious safety problems such as hospitalization occur in the trial and are judged to be treatment-related, the trial steering committee will stop the trial promptlyIf there is serious deviation in the implementation of the clinical trial protocol, the data monitoring committee should discontinue the trial in time

#### Randomization and blinding

Allocation of cases to study groups is undertaken by a person not participating in the trial with the help of the generation of random sequencing using the SAS statistical software. Allocations are placed in sealed envelopes. Participants will be allocated an individual trial identification number. Research assistants will perform the allocation of patients to the study groups by opening of sealed envelopes at the time and prior to the first intervention cycle.

Due to the nature of the intervention, only the principal investigator is blinded to the treatment in this study. Unblinding is permissible only if the intervention is considered necessary to guide clinical management and with the consent of the principal investigator.

### Sample size

The sample size was calculated from SUN’s previous study [16]. The primary outcome was the change of mean defect (MD) value of VF after 8 weeks of treatment compared with baseline. Based on the reference (Sun et al.), the MD value of the treatment group is 2.06 ± 1.73. The MD value of the control group is 0.73 ± 1.93. The difference between the effect values of the treatment period and the control period was 1.43, and the standard deviation of the two periods was 1.93. When a two-tailed test with a test power of 80% and significance level of 5% was applied to the research, 10 cases were calculated [17]. Taking into account of 20% dropout rate, we ultimately identified 12 participants.

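### The planning difference of 1.43 contradicts the printed means (2.06 − 0.73 = 1.33), and 12 enrolled less 20% does not leave the 10 cases required

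*Protocol article*

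**What the plan says.** All the figures are in the protocol article, Methods, Sample size. From an earlier study the article takes the change in MD after 8 weeks: "the MD value of the treatment group is 2.06 ± 1.73. The MD value of the control group is 0.73 ± 1.93". It then says: "The difference between the effect values of the treatment period and the control period was 1.43". On the spread it adds: "the standard deviation of the two periods was 1.93". With a two-sided 5% level and 80% power, "10 cases were calculated". The last step is: "Taking into account of 20% dropout rate, we ultimately identified 12 participants".

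Two other sections bear on how the calculation should be read. Study design gives each patient three treatment/control comparisons. Statistical analysis treats each of a patient's pairs as an independent trial, uses the full analysis set, and handles missing values with a mixed-effects model for repeated measures. The formula itself is not written out; a reference is cited for it.

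**The concern.** Three printed numbers that should satisfy one subtraction do not, so at least one of them is wrong. The one that looks out of line, 1.43, is the larger and more favourable value, and it appears to be the one that produced the sample size. The dropout step is a second, separate slip: the enrolled number does not leave the required number after the stated loss.

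This paragraph is the only justification for the size of a 12-patient trial. As it stands, a reader cannot tell which difference the trial was planned to detect. A null result would be read against a claim of 80% power that may not follow from the trial's own inputs.

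**Working it through.** **Inputs (Sample size section).** Means 2.06 and 0.73; group SDs 1.73 and 1.93; stated difference 1.43; stated SD 1.93; two-sided 5%; power 80%; 10 cases; 20% dropout; 12 enrolled. Three pairs per patient comes from Study design, and independence of pairs from Statistical analysis.

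**Step 1, the subtraction.** 2.06 − 0.73 = 1.33, not 1.43.

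**Step 2, reproducing the plan's 10.** A normal approximation with three independent pairs per patient and SD per period is

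n = 2(z₀.₉₇₅ + z₀.₈₀)²·SD² / (3d²), with (1.96 + 0.8416)² = 7.849.

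At d = 1.43 and SD = 1.93: 2 × 7.849 × 3.7249 / (3 × 2.0449) = 9.53, so 10. This matches the article and fits its design. Other readings at 1.43 and SD 1.93 do not give 10:
- One pair per patient, 1.93 as SD of the difference: 15 (normal) or 17 (t).
- Three pairs, 1.93 as SD of the within-pair difference: 5 (normal) or 7 (t).
- Three pairs, 1.93 per period, t-test on patient means: 12.

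**Step 3, the printed means.** At d = 1.33 and SD = 1.93: 2 × 7.849 × 3.7249 / (3 × 1.7689) = 11.02, so 12 completers.

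**Step 4, dropout.** 10 × 1.2 = 12 reproduces the article's number. But losing 20% of 12 leaves 12 × 0.8 = 9.6. To keep 10 one needs 10/0.8 = 12.5, so 13. If 10 are needed, 12 enrolled tolerates a loss of 2/12 = 16.7%.

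**Step 5, power.** Power ≈ Φ(d/SE − 1.96), with SE = SD·√(2/(3n)). For example, at n = 10 and SD 1.93, SE = 0.498; 1.33/0.498 − 1.96 = 0.71, giving 76.1%.

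| Assumption | 10 completers | 9.6 | 9 |
|---|---|---|---|
| d = 1.33, SD 1.93 | 76.1% | 74.4% | 71.6% |
| d = 1.33, pooled SD 1.83 | 80.3% | 78.6% | 76.0% |
| d = 1.43, SD 1.93 | 81.9% | 80.3% | 77.7% |

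The pooled SD is √((1.73² + 1.93²)/2) = 1.83. With d = 1.33 it gives n = 2 × 7.849 × 3.3589 / 5.3067 = 9.94, so also 10. With all 12 completing, d = 1.33 and SD 1.93 give 83.2%.

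**Step 6, detectable difference.** At 80% power, SD 1.93 and 9.6 completers: 2.8016 × 1.93 × √(2/28.8) = 1.42.

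**The case against.** The strongest objection is that the direction of the slip is unknown. A difference of 0.10 could equally lie in a mean (2.16 or 0.63 would give 1.43), and the source study is not at hand. If 1.43 is right, 10 is right under the apparent formula and power after dropout is close to 80%. This stands, so the loss of power must be stated as conditional.

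A second route also leads to 10: the pooled SD with d = 1.33. On that reading only the printed 1.43 would be wrong. It cannot be excluded, because the formula is not shown. But the text names 1.93 as the SD, and even on this route power after 20% dropout is 76–79%.

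The dropout slip is small, and multiplying by 1.2 is a common shortcut. Under the planned mixed model, a patient who leaves after a complete cycle still contributes data, so counting every dropout as a total loss is a worst case. That softens the consequence. It does not make 9.6 equal to 10.

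A reader might infer worse: that the trial needs 15 or more completers, from a single-pair calculation, or that power is only 60–66%, from a t-test on patient means with 9 or 10 completers at d = 1.33. The documents do not support either as the plan's own figure. The first ignores the three-pair design. The second is not the stated analysis, which treats pairs as independent; a t-test on 30 such pairs gives about 73% at d = 1.33 with 10 completers. Whether pairs should be treated as independent is a different question. In the other direction, reading 1.93 as the SD of the within-pair difference over three pairs would give about 97% power at d = 1.33 with 10 completers, but that reading does not reproduce 10 cases.

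**Conclusion.** The Sample size paragraph is wrong as written. The stated difference contradicts the printed means by 0.10, and the dropout step leaves 9.6 of the 10 cases required. Both hold without any assumption about the formula.

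The effect on power is conditional. It rests on the three-pair normal formula, inferred because it reproduces 10, and on which number proves right. If the means and SD 1.93 stand, the trial falls short of 80% by about 4 points with 10 completers and by about 6 to 8 points with 9.6 or 9. If 1.43 stands, the shortfall is at most about 2 points, and only at 9 completers. It would go too far to say outright that the trial lacks 80% power: the documents show that the claim does not follow from the printed inputs, not which input is wrong.

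**What to change.** Check the cited source study and correct either the means or the difference. Write out the formula, say that it counts three pairs per patient, and say which SD enters it (per period, pooled, or within-pair difference). Then restate power or detectable difference for 12 enrolled with 20% dropout, using the corrected inputs.

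If 1.33 and SD 1.93 are confirmed, that statement would be about 72–74% power under the normal formula, or 80% power for a difference of about 1.42 with 9.6 completers. These figures should not go in before the source check.

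Correct the dropout sentence in the same paragraph: 20% of 12 leaves 9.6. If 10 completers remains the requirement, 12 enrolled allows a loss of 16.7%. If the source check raises the requirement to 12 completers, 12 enrolled allows none.

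The cost is rewording one paragraph and, probably, a less favourable stated power. Enrolment, endpoint and analysis need not change.
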